# 4.2 Study design

The study will be a cluster-randomized controlled trial. A study cluster will be defined as the catchment area of a community health post. CHWs work from a community health post with well defined catchment area and population within a health facility catchment area and are supervised by the staff of the health facility. The clusters (community health post catchment area) will be matched in pairs according to the health facility catchment area they belong to, the distance from the health facility and the population size. Randomization will then be done from among the matched clusters to select the intervention and the control arms. CHWs in both the intervention and control arms will receive training in the assessment and classification of children presenting with fever and/or cough/difficult breathing. The CHWs in the intervention arm will be supplied with RDTs, Coartem® and amoxicillin. The intervention CHWs will be trained to use RDTs in patients with reported fever and provide those with a positive result with Coartem while patients suspected of pneumonia (based on fast breathing) will be treated with amoxicillin as per the standard of care at health facilities and monitored. Those with negative RDT result will be treated with antipyretic and asked to return if they do not get better after 48 hours or condition deteriorates. In the control group, no RDT will be performed. The CHWs will be supplied with Coartem to treat malaria/febrile illness as per the IMCI guidelines and patients suspected of pneumonia will be referred to the health facility for treatment as per the current practice. The supply of the drugs and RDTs will come through the normal MOH sources. The study will utilize specialized field workers (data collectors and data supervisors) to visit CHWs to collect data on their consultations and follow-up children treated by CHWs. Consent will be sought from caregivers to allow us collect data by which to assess the effectiveness of the intervention. Caregivers in both the intervention and control arms are not obliged to receive care from the CHWs. They are free to go to any of the health facilities in the study area instead of a CHW. The study will collaborate with the MOH and the DHMTs to ensure that the health facilities in the study area have RDTs, Coartem and amoxicillin.

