**4.3 Sample Size**

This study will be a cluster randomized trial at the level of the community health post. As a result, we need to take the intracluster correlation within individuals receiving treatment at each community health post in both the calculation of sample size and data analysis.

The two primary study hypotheses were stated earlier: one for the treatment of children with fast breathing and one for the treatment of children with fever. We will calculate a sample size for each of the study hypothesis

There are 43 community health posts in the study area. This will be a two-arm study so we will have 21 community health posts available for each arm with a 1:1 allocation. All of the calculations are made using the assumption of 80% power to show differences and a two side alpha of 0.05.

The sample size for a cluster randomized trial is based upon the intracluster coefficient (ICC). As we do not have accurate information on the expected ICC for the outcomes in this study, the sample size is presented as a series of sample size calculations given a range of the ICC values which we would expect to see.

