**6.0 Statistical Analyses**

# 6.1 Primary end-points comparison

There are two primary endpoints for the study depending upon whether a child has fever or fast breathing. For children with fever the primary outcome is appropriate treatment with Coartem® and for children with fast breathing the primary outcome is early and appropriate treatment. For each primary outcome, crude proportions in the two groups will be compared using the Mantel-Haenszel chi-square test with clusters as strata to account for the cluster randomization. Crude data will be presented as cluster adjusted odds ratios and 95% confidence intervals. Inferences about treatment effects will be made at the level of the individual not at the level of the cluster. Analyses will be based on an intent-to-treat basis.

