# 6.2 Secondary end-point comparison

The secondary outcomes are:

1. To measure the proportion of children managed in each study arm who does not respond to treatment (treatment failures).
2. To measure the cost-effectiveness of having CHWs manage presumptive malaria using Coartem® with and without the use of RDTs.
3. To measure the proportion of acute febrile illnesses in children which are RDT-positive.

The analysis of the secondary outcomes 1 and 3 would be similar to the analysis of the primary outcomes. The analysis of secondary outcome 2 is described below.

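### The crude test of both primary outcomes stratifies by cluster, but every cluster lies wholly in one arm, so the Mantel-Haenszel statistic and its odds ratio are 0/0; the planned GEE is unaffected

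*Protocol*

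**What the plan says.** Section 4.2 fixes the unit: "A study cluster will be defined as the catchment area of a community health post". Clusters "will be matched in pairs according to the health facility catchment area they belong to", and also by distance from the facility and population size. Then "Randomization will then be done from among the matched clusters to select the intervention and the control arms". Section 4.3 states that "we will have 21 community health posts available for each arm with a 1:1 allocation".

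Section 6.1 specifies that, for each primary outcome, crude proportions will be "compared using the Mantel-Haenszel chi-square test with clusters as strata to account for the cluster randomization", and adds: "Crude data will be presented as cluster adjusted odds ratios and 95% confidence intervals". It also says that inference is directed at the individual rather than the cluster and that analysis is by intention to treat.

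Under its multivariable regression heading, the same section plans a GEE with robust standard errors and a compound-symmetry working correlation. This GEE adjusts the final results for clustering and confounders.

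Section 6.2 states: "The analysis of the secondary outcomes 1 and 3 would be similar to the analysis of the primary outcomes". Outcome 1 is treatment failure. Outcome 3 is RDT positivity, which exists only in the intervention arm and so involves no comparison of arms.

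**The concern.** Stratifying by a factor removes every comparison between levels of that factor. When the cluster is both the unit of randomisation and the stratum, the treatment contrast lies entirely between strata, and stratification removes all of it. The protocol gives accounting for the cluster randomisation as the reason for this test, but the test has no treatment comparison left to make.

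The only unadjusted comparison named for the two primary outcomes and for treatment failure therefore returns nothing. A replacement would have to be settled later, possibly with data in hand. The nearest rewording, matched pairs as strata for individual children, would run but would still treat children within a post as independent.

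**Working it through.** **Inputs.** Cluster definition, pairing and whole-cluster allocation: section 4.2. Test and effect measure: section 6.1. Two-sided alpha 0.05 and 80% power: section 4.3. Fast-breathing configuration: 38 clusters × 12 children = 456, with 50% v 70%, from the last row of the first table in section 4.3. The ICC values 0.05 to 0.25 are the ends of the table's range.

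**The plan's own figure.** The protocol gives no figure for the Mantel-Haenszel test itself. The nearest is the 456. It reproduces from the formula for pair-matched clusters if the column labelled ICC is entered as a between-cluster coefficient of variation k:

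clusters per arm = 2 + (1.96 + 0.84)² × {[p1(1−p1) + p2(1−p2)]/m + k²(p1² + p2²)} / (p1−p2)²

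= 2 + 7.849 × {(0.25 + 0.21)/12 + 0.0625 × (0.25 + 0.49)} / 0.04 = 18.6, rounded up to 19.

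That gives 38 clusters and 38 × 12 = 456. The same formula returns all 22 rows of the two tables. How that column is labelled is a separate matter. What matters here is that the sizes agree with a paired, cluster-level comparison.

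**Step 1: clusters as strata.** For one stratum of size n, let a and b be intervention children with and without the outcome, and c and d the same for control. Let n1 = a + b, n0 = c + d, m1 = a + c and m0 = b + d.

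- Odds ratio = Σ(ad/n) / Σ(bc/n)
- Chi-square = [Σ(a − n1·m1/n)]² / Σ{n1·n0·m1·m0 / [n²(n−1)]}

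| Stratum | ad/n | bc/n | a − E(a) | Var(a) |
| --- | --- | --- | --- | --- |
| Intervention post (c = d = 0) | 0 | 0 | a − a = 0 | 0, as n0 = 0 |
| Control post (a = b = 0) | 0 | 0 | 0 − 0 = 0 | 0, as n1 = 0 |

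Summed over any number of posts, the odds ratio is 0/0 and the chi-square is 0/0. Effect size, ICC and cluster size do not enter. A numerical check with 38 one-arm tables of 12 children (70% v 50%) gave all four sums as 0, and standard software returned no value for either quantity. Intention to treat keeps each child in the post's arm, so crossover cannot create a two-arm stratum.

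**Step 2: matched pairs as strata.** This test is not in the protocol. It is examined because it is the closest computable wording. Each stratum now holds one post per arm, so the statistic exists. The setting was no true effect, 19 pairs, 12 children per post, a 50% rate, beta-distributed post rates and nominal two-sided 5%. The documents do not say how much between-post variance the matching removes, so three assumed values are shown.

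| ICC | Matching removes none | Half | 80% |
| --- | --- | --- | --- |
| 0.05 | about 12% | about 8% | about 6% |
| 0.10 | about 20% | about 13% | about 9% |
| 0.25 | about 34% | about 24% | about 13% |

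Entries are rejection rates and move by about one percentage point between simulation runs. A paired t-test on post-level proportions rejected about 5% of the time in every cell.

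**The case against.** **The GEE supplies the inference.** This largely stands. Section 6.1 plans a GEE with robust standard errors for the final results. It uses the cluster as the correlation unit and can be estimated. A reader might infer from the empty test that the trial has no usable primary analysis, but the documents do not support that. The same holds for treatment failure, since an analysis similar to the primary one includes the GEE. What remains is that the GEE is specified as the confounder-adjusted analysis, and the crude comparison beside it cannot be produced.

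**The false-positive rates belong to a test the protocol does not name.** This also stands. Section 6.1 says clusters, not pairs. A reader might infer that the plan as written carries a 34% type I error, but as written it yields no test result at all. The 34% also assumes that matching on facility, distance and population size achieves nothing. The figures cover only the fast-breathing configuration and show only why the nearest rewording is not a repair.

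**Cluster may have been used loosely.** Section 4.9 assigns 12 data collectors at 2 per cluster, which implies six units. Section 4.1 lists six health centres (one affiliated to the hospital and five rural). Facility-area strata would contain both arms and be computable. But section 4.2 carries the formal definition, and a facility-stratified test on individual children would still ignore correlation within posts.

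**A cluster-level test conflicts with the stated level of inference.** Correct: section 6.1 directs inference at the individual. The fix must amend that sentence if it uses a cluster-level test.

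**Conclusion.** The point holds for the crude comparison. Under the definitions in section 4.2, the Mantel-Haenszel test and the crude odds ratio of section 6.1 are 0/0 for both primary outcomes, and section 6.2 extends this to treatment failure. The result is algebraic and rests only on whole clusters being allocated to one arm. It is not something a statistical analysis plan could fill in, because the protocol names a specific method that cannot work. The adjusted GEE is unaffected.

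Matched pairs as strata on individual data would not meet the section's stated purpose. Under the working assumptions its type I error is about 6–12% at ICC 0.05 and 13–34% at ICC 0.25, the lower end if matching removes 80% of between-post variance and the upper end if it removes none.

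**What to change.** In section 6.1, and for treatment failure in section 6.2, delete the Mantel-Haenszel test with clusters as strata. Replace it with a crude comparison that respects the unit of randomisation:

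- **Preferred:** a paired t-test or paired permutation test on within-pair differences in post-level proportions, reported as a risk difference with 95% CI. State the change of crude effect measure from odds ratio to risk difference, and amend the sentence on individual-level inference to match.
- **If an odds ratio is to be kept:** the GEE of section 6.1 fitted without covariates. This is the smaller edit and leaves the sentence on individual-level inference as it is. One caution concerns fever. Section 4.3 plans on 100% Coartem use in controls. If every control child is treated, the odds ratio for that outcome has no finite estimate, whereas a risk difference does.

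Keep the covariate-adjusted GEE as the adjusted analysis in either case. The cost is a few sentences in sections 6.1 and 6.2, with no new data and no additional children.

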# Confounding

Because this is a cluster-randomized trial, the potential for confounding is greater than in an individually randomized trial. To adjust for this we will collect data on predictors of inappropriate treatment within clusters. Independent predictors of inappropriate treatment will be used to adjust for confounding in the final regression analysis.

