#### 4.14 Follow-up

The patients seen by the CHWs with fever and/or fast breathing will be followed up at home by the data collectors to assess the outcome of the treatment given or recommended. The follow-up visit will occur 5-7 days after the visit to the CHW. The data collectors will make contacts with CHWs at least every other day to take particulars of children treated from the identification and baseline forms in order to schedule a follow-up visit. During the follow-up visits, the data collectors will interview the caregiver (the person who took the child to see the CHW or in his/her absence a family member who knows sufficiently about the illness and the care received); and perform some basic examination including taking of temperature and counting of respiratory rate. Information that will be collected during the follow-up visits will include, complaints that prompted heath seeking at the CHW, treatment given, counseling or advice given, referrals, self-reported adherence to the medication, outcome of the visitation, alternative treatment after the visit and where such alternative treatment was obtained and current general condition and complaints. They will also be asked questions to explain inappropriate treatment. If a subject is found not to be improving, the data collector will advise the caregiver to go to the clinic.

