# Multivariable regression

To account for the clustering as well as to adjust for potential confounding, we will adjust the final results using a multivariable regression model. We will use generalizing estimating equations (GEE) 24 to estimate the log odds of the intervention on inappropriate treatment proportion compared to the control group. Use of GEE will allow us to adjust variance estimates (providing robust standard errors) to account for the clustering of cases within a cluster. The correlation matrix will be defined as compound symmetry. Odds ratios and 95% confidence intervals will be used to summarize the data.

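### The covariate rule for the final GEE admits variables that the intervention may affect and does not guarantee the matching factors a place; fix both in advance.

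*Protocol*

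**What the plan says.** The Protocol's section 6.1 sets the covariate rule under Confounding. It notes that confounding is a greater risk in a cluster-randomised trial and continues: "To adjust for this we will collect data on predictors of inappropriate treatment within clusters". It then states how those data are used: "Independent predictors of inappropriate treatment will be used to adjust for confounding in the final regression analysis".

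Under Multivariable regression the final model is a GEE with compound symmetry and robust standard errors: "To account for the clustering as well as to adjust for potential confounding, we will adjust the final results using a multivariable regression model". Its outcome is inappropriate treatment.

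Section 4.2 says that the health post catchment areas "will be matched in pairs according to the health facility catchment area they belong to, the distance from the health facility and the population size", and then: "Randomization will then be done from among the matched clusters to select the intervention and the control arms". Neither the pairs nor these three factors are mentioned in section 6.1.

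Section 4.14 lists what is collected at the home visit 5–7 days after the contact with the community health worker (CHW): treatment given, referrals, self-reported adherence and alternative treatment. It adds: "They will also be asked questions to explain inappropriate treatment". Section 5.1 gives a similar list for the same visit.

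**The concern.** Two features of the rule deserve attention.

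First, a variable qualifies by predicting the outcome, and no restriction keeps out variables that the arm can change. The arms differ by design in whether suspected pneumonia is treated at the post or referred, and in whether an RDT is used. Several variables recorded after the contact are therefore plausible steps between assignment and early, appropriate treatment, and for that reason plausible strong predictors of it. Adjusting for such a step removes the part of the effect that runs through it.

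Second, the factors that structured the randomisation are left to chance selection. If they are related to outcome and are not selected, the precision that matching was meant to provide is not recovered, and the intervals are wider than they need be.

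The rule governs what the Protocol calls the final results, so both features bear on the primary comparison.

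**Working it through.** **1. What the sample size assumed.** Section 4.3 states: "All of the calculations are made using the assumption of 80% power to show differences and a two side alpha of 0.05". For fast breathing it plans 50% v 70% and, at a tabulated coefficient of 0.25, 38 clusters of 12, or 456 children.

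- Usual design effect: 93 children per arm before clustering; 1 + (12 − 1) × 0.25 = 3.75; 2 × 93 × 3.75 ≈ 698. This does not give 456.
- Pair-matched cluster formula, reading the tabulated value as a between-cluster coefficient of variation k: pairs = 2 + (1.96 + 0.842)² × [p0(1−p0)/m + p1(1−p1)/m + k²(p0² + p1²)] / (p0 − p1)². The bracket is 0.25/12 + 0.21/12 + 0.0625 × 0.74 = 0.0846. Then 7.849 × 0.0846 / 0.04 = 16.60. Adding 2 gives 18.60, so 19 pairs, 38 clusters and 456 children.
- The unmatched version adds 1 instead of 2: 17.60, so 18 per arm, or 36 clusters.

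The pair-matched version reproduces all 22 rows of the two tables. The unmatched version is two clusters short in every row. The sizing thus fits a matched design that section 6.1 does not mention.

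**2. Adjusting for a variable on the causal path.** The planned effect is an odds ratio of (0.70/0.30)/(0.50/0.50) = 2.33. (Coded as inappropriate treatment it is the reciprocal; attenuation is toward 1 either way.) The fever outcome is not used here, because its planned control rate of 100% gives no finite odds ratio.

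The Protocol names no mediator, so these inputs are assumptions: a binary variable present in 40% of control and 80% of intervention children, and a share s of the 20-point effect passing through it. The mediator then raises the success probability by 0.20s/0.40, and the direct effect is 0.20(1 − s). The last column is a simulated exchangeable logistic GEE with 38 clusters of 12 and 150 runs per row.

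| s | Control, mediator absent / present | Intervention, absent / present | OR within absent / present | Simulated adjusted OR |
|---|---|---|---|---|
| 0 | 0.50 / 0.50 | 0.70 / 0.70 | 2.33 / 2.33 | 2.41 |
| 25% | 0.45 / 0.575 | 0.60 / 0.725 | 1.83 / 1.95 | 1.96 |
| 50% | 0.40 / 0.65 | 0.50 / 0.75 | 1.50 / 1.62 | 1.63 |
| 75% | 0.35 / 0.725 | 0.40 / 0.775 | 1.24 / 1.31 | 1.29 |
| 100% | 0.30 / 0.80 | 0.30 / 0.80 | 1.00 / 1.00 | 0.97 |

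The unadjusted estimate stayed at 2.31–2.43. Simulated power fell from 95–98% unadjusted to about 81, 53, 20 and 9% for shares of 25, 50, 75 and 100%. The simulated values differ slightly from the within-stratum ones because of finite samples and Monte Carlo error.

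**3. Leaving the matching out.** Let r be the within-pair correlation of cluster outcomes, which the Protocol does not give. If the pairs are ignored altogether, the standard error is multiplied by 1/√(1 − r). With 19 pairs, where the matched test has 80% power, cluster-level simulation gives:

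| r | SE ratio | Power ignoring pairs | Actual two-sided size |
|---|---|---|---|
| 0.1 | 1.05 | 79% | 0.040 |
| 0.2 | 1.12 | 75% | 0.030 |
| 0.3 | 1.20 | 70% | 0.022 |
| 0.5 | 1.41 | 54% | 0.008 |

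Ignoring the pairs costs nothing below r = 1 − (2.028/2.101)² ≈ 0.07, because the unmatched test has more degrees of freedom. The error is conservative.

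**4. Pair indicators as a remedy.** With one indicator per pair, each cluster residual is half the centred within-pair difference. The uncorrected robust variance is then about (P − 1)/(2P) of the right value. For 21 pairs this is 20/42 = 0.476, and 1.96 × √0.476 = 1.35. On 20 degrees of freedom that cut-off is exceeded about 19% of the time under the null. Logistic simulations with 42 clusters of 12 gave 18–23%, against about 7% with the matching factor as a covariate and 3.5% with neither.

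**The case against.** The section's purpose is to correct for confounding, and a consequence of the arm is not a confounder. On a sympathetic reading, the predictors are meant to be baseline ones and the list belongs in a statistical analysis plan. No mediator is named, and the Confounding text does not refer to the day 5–7 questions. This has weight and limits the conclusion to what could happen. It does not remove the point: the Protocol states a selection rule, the rule has no such limit, and the home visit asks for explanations of the very outcome being modelled.

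A reader might infer that the adjusted analysis will drive the odds ratio to about 1, for example by adjusting for antibiotic availability at the post. The documents do not support that. Amoxicillin at the post is nearly the same thing as the arm, so the model could hardly separate the two; and attenuation is zero if nothing selected is on the path.

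A reader might also infer that precision is certainly thrown away. That goes too far. A matching factor that predicts the outcome could be selected under the stated rule. In a simulation with 42 posts of 12 children (assumed intracluster correlation about 0.15, one matching index explaining 25% or 50% of between-post variance, ten baseline candidates selected at p < 0.05), the standard errors were 0.267 and 0.246. They were 0.265 and 0.244 with the index forced in. Omitting it altogether widened intervals by about 6% and 15%.

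Nor does selection among baseline candidates by itself wreck the intervals: type I error was 6.3–8.3%, against 5.5–6.9% with the matching factor fixed.

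**Conclusion.** The point holds in conditional form. The rule selects covariates by their relation to the outcome, does not exclude variables that assignment can affect, and coexists with data collection that supplies such variables. If one on the causal path is selected, the adjusted odds ratio is biased toward 1. The size depends wholly on the mediated share: from no attenuation of 2.33 to about 0.97 in the illustration, whose 40% v 80% prevalence is assumed.

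The matching factors have no guaranteed place in the model although the sizing fits only a pair-matched calculation. Any resulting loss is of precision, in the conservative direction, and arises only if matching was effective (r above about 0.07 with 19 pairs) and the factors are not selected. The documents do not show that a mediator will be adjusted for or that precision will in fact be lost. The change is worth making because it is cheap and removes both possibilities.

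**What to change.** Replace the last sentence under Confounding with a rule to this effect. The adjusted GEE includes the matching factors (health facility area, distance, population size) as covariates, plus a short list of baseline covariates such as child age, all fixed before outcome data are seen. No variable that assignment could affect is adjusted for. Predictors selected from the data appear only in a sensitivity analysis. Wording the bar as what assignment could affect, not as what is measured after randomisation, keeps child age, which is recorded at presentation.

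Under Multivariable regression, add a small-sample correction to the robust standard errors. Do not enter pair indicators with uncorrected robust standard errors.

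Cost: a few sentences. The matching variables must already exist to form the pairs. The downside is degrees of freedom with about 42 clusters: if the areas are those of the six health centres in section 4.1 (an assumption), facility area takes five, and distance and population size one each, so seven in all.
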